#### 2.2.2. Exclusion Criteria

Participants meeting any of the following criteria will be excluded: (1) age > 42 years old; (2) antral follicle count (AFC) <  3 measured on day 2 of the cycle; (3) multiple unsuccessful stimulation cycles ending with cancellation; (4) allergy to medications used for ovarian rejuvenation; (5) three or more ovarian surgeries result in significant ovarian reserve depletion (iatrogenic POI, iatrogenic DOR); (6) secondary amenorrhea; (7) uterine developmental abnormalities; and (8) inability to engage in physical activity.

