#### 2.3.1. Primary Outcome

The primary outcome is the change in FSH and AMH levels compared with the levels before. Spontaneous pregnancy during the study period will be recorded as a primary outcome measure.

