### 2.7. Implementation

The principal investigator or a designated sub-investigator will input the required data into a web-based allocation system for eligible patients. Subsequently, the system will allocate participants to the three investigated groups. The required data include personal data, demographic data, medical and family history, body composition assessment (weight, height, BMI), menstrual cycle (length and days of menstruation), hormone levels (AMH, FSH, LH, E2, PRL, TSH, vitamin 25-OH-D3), progesterone levels, and the FSFI questionnaire, as shown in Table 1.

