### 4.6. Baseline Assessments

Baseline assessments will adhere to the trial’s standard operating procedure (SOP). During the first visit, between days 2 and 4 of the cycle, a laboratory examination will be conducted, including hormone levels of AMH, FSH, LH, E2, PRL, TSH, 25-OH-D3 vitamin, and progesterone. Baseline progesterone will be measured between days 21 and 22 of the same cycle. The FSFI questionnaire will also commence during this phase.

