### 4.7. Efficacy Assessments

The efficacy of the trial treatment will be evaluated using a comprehensive set of parameters measured at the 3-month follow-up. Participants’ weight, height, and BMI will be recorded. This will help in assessing any changes in body composition resulting from the intervention. The regularity and characteristics of participants’ menstrual cycles will be monitored from the start to the end of the study. This continuous observation aims to identify any improvements or alterations in menstrual health. Hormonal evaluations, including levels of AMH, FSH, LH, E2, PRL, TSH, and 25-OH-D3 vitamin, will be conducted at the conclusion of the study as well. As a primary outcome, the change in FSH and AMH levels will be administered. The measurement of progesterone will help evaluate the sufficiency of the luteal phase, which is critical for reproductive health. These measures will provide insights into the hormonal balance and ovarian function of the participants. The FSFI questionnaire will be administered to assess changes in sexual function. This self-reported measure will provide valuable data on the impact of the intervention on participants’ sexual health. The occurrence of spontaneous pregnancy during the study period will be recorded as a primary outcome measure. This will directly indicate the effectiveness of the intervention in improving fertility. These comprehensive assessments will collectively provide a thorough evaluation of the intervention’s efficacy.

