## Figures and Tables

**Figure 1 life-15-00018-f001:**
[figure not shown]
Trial design.

**Table 1 life-15-00018-t001:** Study Assessments and Procedures.

	Screening	Baseline (2–4. Day of Menstrual Cycle)	Baseline (21–22. Day of the Same Cycle)	3 Months (2–4. Day of Cycle)	3 Months (21–22. Day of the Same Cycle)
Assessment					
Investigator meetings	✓				
Informed consent	✓				
Demographics, medical, and family history	✓				
Body composition assessment (Weigh, Height, BMI)	✓			✓	
Menstrual cycle	✓			✓	
Hormone levels (AMH, FSH, LH, E2, PRL, TSH, 25-OH-D3 vitamin)		✓		✓	
Progesteron		✓	✓		✓
FSFI questionnaire		✓		✓	
Spontaneous pregnancy				✓	

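### The pregnancy outcome has no stated start, so conceptions in the baseline cycle, before treatment, can be counted as primary-outcome events

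*Protocol article*

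**What the plan says.** - **Outcome.** Section 2.3.1: "Spontaneous pregnancy during the study period will be recorded as a primary outcome measure". No start is given (screening, baseline, allocation or first treatment). Table 1 ticks pregnancy once, at 3 months.
- **Interpretation.** Section 4.7 says of the pregnancy count: "This will directly indicate the effectiveness of the intervention in improving fertility".
- **Baseline schedule.** Section 4.6 puts two samples in one cycle: "During the first visit, between days 2 and 4 of the cycle, a laboratory examination will be conducted", and then "Baseline progesterone will be measured between days 21 and 22 of the same cycle". Table 1 gives the later sample its own column, labelled "Baseline (21–22. Day of the Same Cycle".
- **Order of allocation.** Section 2.7 lists the data to be entered for an eligible patient, ending with "progesterone levels, and the FSFI questionnaire, as shown in Table 1". Just before that list it says: "Subsequently, the system will allocate participants to the three investigated groups".
- **Eligibility.** Neither the inclusion list (2.2.1) nor the exclusion list (2.2.2) mentions pregnancy at entry or contraception during baseline, and Table 1 schedules no pregnancy check before 3 months.
- **Duration.** Section 2.6 gives participation as about 12 weeks; section 4.1 gives the exercise programme as at least 3 months.

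**The concern.** The women are infertile patients (section 2.6), and the Introduction defines infertility by regular unprotected intercourse and expects spontaneous pregnancies. Conception in the baseline cycle is therefore a real possibility. Menstruation at the day 2–4 visit argues against pregnancy on that day, but not against conception two weeks later.

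If allocation and treatment follow the day 21–22 sample, a woman may already have conceived when she is randomised. Her pregnancy is found at 3 months and counted for an arm whose treatment she had not begun. Under section 4.4, item 3, she also leaves trial treatment with little or no exposure. At stake is what a primary outcome measures: part of the count would be background conception that no arm could have influenced.

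**Working it through.** **1. The plan's own figure.** The sample size is not in question. One-way ANOVA with three groups, f = 0.4 and alpha 0.05 gives power 0.949 at N = 99 and 0.955 at N = 102, so 102 is the smallest balanced total that reaches 0.95. With 15% dropout, 34/0.85 = 40 per group, or 120. Both stated figures reproduce, and the fix does not change them.

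**2. Order of events.** Section 2.7 names progesterone separately from the hormone panel, refers to Table 1, and puts allocation after data entry. Table 1 has two baseline progesterone entries, on days 2–4 and days 21–22. The natural reading is that both precede allocation. This is an inference, because a day 2–4 value alone would satisfy the words of 2.7. The baseline label on the later sample points the same way: if treatment began right after days 2–4, that sample would be taken 21 − 4 = 17 to 22 − 2 = 20 days into treatment.

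**3. Size.** The article gives no conception rate, so the per-cycle probability p is an assumption, varied from 1% to 8%. Assume one untreated baseline cycle followed by three treated cycles (12 weeks = 84 days = 3 × 28) and 40 women per arm, with q the per-cycle probability under treatment.

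- Counted from treatment: 1 − (1 − q)³
- Counted with the baseline cycle: 1 − (1 − p)(1 − q)³
- Share predating treatment with no effect (q = p): p / [1 − (1 − p)⁴]

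Worked at p = 3%:

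- No effect: 120 × (1 − 0.97⁴) = 120 × 0.1147 = 13.8 pregnancies, of which 120 × 0.03 = 3.6 predate treatment; 3.6/13.8 = 26%.
- Treatment doubles the rate (q = 6%), counted from treatment: 1 − 0.94³ = 16.9% against 1 − 0.97³ = 8.7%; ratio 1.94, difference 8.2 points.
- The same, with the baseline cycle: 1 − 0.97 × 0.94³ = 19.4% against 11.5%; ratio 1.69, difference 8.0 points.

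Over the range:

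| Assumed p | Baseline-cycle conceptions, of 120 | Share of count, no effect | Risk ratio if doubled: from treatment → with baseline cycle |
|---|---|---|---|
| 1% | 1.2 | 25% | 1.98 → 1.73 |
| 3% | 3.6 | 26% | 1.94 → 1.69 |
| 5% | 6.0 | 27% | 1.90 → 1.66 |
| 8% | 9.6 | 28% | 1.84 → 1.60 |

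The risk difference is multiplied by exactly (1 − p), which is why it hardly moves. The chance of at least one such conception among 120 women, 1 − (1 − p)¹²⁰, is 70% at 1% and 97% at 3%. Per arm of 40 the expected number is 0.4 to 3.2, so chance imbalance of one or two events is plausible.

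**The case against.** - **Allocation after days 21–22 is not stated.** True. Nor is the start of treatment dated. If treatment began at the next menstruation and the count began with treatment, a woman who conceived in the baseline cycle would not be counted. The 12 weeks in section 2.6 and the discontinuation rule in section 4.4 can be read that way. A reader might infer that one of the two measures, pregnancy or baseline progesterone, must be wrong whichever order applies. The article does not support that, because an order exists in which both are sound. It does not state that order, however, and the count in 2.3.1 is not tied to treatment.
- **Randomisation balances these conceptions.** It does, in expectation. A reader might infer bias towards an arm or a false-positive risk; neither follows. Dilution of the ratio, inflated percentages and chance imbalance remain.
- **The comparison has little power anyway.** At p = 3% with doubling and 40 per arm, two-sided Fisher power is about 12% without the baseline cycle and 11% with it. The counting rule would rarely change a test result. That limits the weight of the point, but not the need for the reported percentages to mean what section 4.7 says they mean.
- **An article may leave a counting rule to fuller documents.** This would settle the matter if the article were merely silent. Here it states the outcome, the baseline schedule, the allocation order and the interpretation, and together these admit events that treatment could not have caused.
- **A mislabelled progesterone baseline matters little.** Agreed: progesterone is neither a primary nor a secondary outcome in 2.3.1 and 2.3.2.

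**Conclusion.** The concern holds as a badly fixed outcome window. As written, the count can include conceptions that predate treatment, and section 4.7 then credits them to the intervention. On assumed rates of 1–8% per cycle, such events would make up about a quarter of the count if there were no effect, and would take a true doubling of the per-cycle rate down to a risk ratio of 1.60–1.73 instead of 1.84–1.98. The risk difference is nearly unchanged, no arm is favoured, and type I error is unaffected.

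The size rests on a constant per-cycle rate, one baseline cycle before three treated ones, and allocation after days 21–22, which is the most natural reading but an inferred one. If treatment in fact starts before days 21–22, the early-conception problem shrinks and the remaining fault is a progesterone value wrongly labelled as baseline, which is minor.

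**What to change.** 1. Reconcile sections 2.6, 2.7, 4.1 and 4.6 with Table 1 on when allocation and treatment start relative to the day 21–22 baseline sample. This must come first: if allocation and treatment prove to start early in the baseline cycle, the rule in step 2 would discard treated time and would need a different anchor.
2. In section 2.3.1, count as primary-outcome events only pregnancies whose last menstrual period began after allocation.
3. Report baseline-cycle conceptions separately by arm.
4. Give the pregnancy comparison with all randomised women in the denominator, alongside any analysis that leaves out women who conceived in the baseline cycle. Leaving them out is not assured to be unbiased. They are identified by whether they menstruate after allocation, and in an open-label trial whether an early conception persists is itself a post-allocation event.
5. If treatment does start before days 21–22, drop the baseline label from that progesterone value.

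The cost is a few sentences and slightly fewer countable events. No new visit is needed, since section 4.7 already has menstrual cycles monitored from the start to the end of the study.

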Despite these promising findings, further research is needed to confirm these effects due to the limited number and sample size of previous studies and the current ambiguity in exercise recommendations for improving fertility outcomes.

In this study, we present a novel and innovative therapeutic exercise protocol specifically designed for pelvic region rehabilitation and ovarian rejuvenation. The therapeutic exercises focus on improving fertility, rehabilitation of the pelvic region (including re-education of the pelvic floor muscles), teaching correct posture, improving the pelvic-lumbar core stabilization system, restoring optimal muscular function of the diaphragm, and activating the parasympathetic nervous system through learning stress-relieving breathing and relaxation. These exercises are expected to enhance pelvic circulation and improve muscle function, which are crucial for reproductive health, especially in patients with diminished ovarian reserve (DOR).

The primary objective of this study is to assess the ovarian rejuvenating effect of this specific exercise program before IVF/ICSI cycles or spontaneous pregnancy, confirming the reproductive efficacy of this regimen. We also aim to improve stimulation and oocyte quality in patients who meet the inclusion criteria, partly by improving pelvic and ovarian circulation (ovarian rejuvenation exercise, the subject of this study) and partly by enhancing cumulus corona radiata and granulosa cell function (per os rejuvenation therapy).

It is expected that our results will show that AMH will be increased, basal FSH levels will be decreased, cycle length will be optimized (getting closer to 28–30 days), fertility rates and stimulation will be improved, and spontaneous pregnancy will be detected at the end of the process. If this investigation confirms the efficacy of the specific exercise program in DOR patients, this could make a useful contribution to fertility treatment in this poorly manageable patient population.

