### 2.2. Eligibility Criteria

#### 2.2.1. Inclusion Criteria

Participants who meet the following inclusion criteria will be included: (1) female of reproductive age 20–42 years; (2) BMI: 18.5–30 kg/m^2^; (3) regular menstruation; (4) anti-Müllerian hormone (AMH) <  1.1 ng/mL; (5) hormone levels: TSH < 2.5 mIU/mL, vitamin D3: >75 nmol/L, Prolactin: <24 ng/mL; (6) understanding the study design, risks, and benefits, and providing informed consent; and (7) the ability to comply with the study protocol.

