### 2.6. Recruitment

Patients meeting the eligibility criteria will be recruited from the Assisted Reproduction Center of Semmelweis University, Hungary. Detailed information about the study will be provided verbally and in writing by the examining physician. Research subjects are informed that in this clinical trial we intend to compare three groups of infertile women. The group receiving only per os complementary therapy, the group receiving per os complementary therapy and walking, and the group receiving per os complementary therapy and a specific exercise program will be tested. We will also inform prospective participants that participation in the research is voluntary and that the anonymized data obtained will be summarized and subjected to statistical analysis. Participation in the study will take approximately 12 weeks.

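### Spontaneous pregnancy is a primary outcome, but eligibility does not exclude women with a known absolute barrier to natural conception, which dilutes the pregnancy comparison

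*Protocol article*

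**What the plan says.** Section 2.3.1 names change in FSH and AMH as primary and adds: "Spontaneous pregnancy during the study period will be recorded as a primary outcome measure". Section 4.7 repeats this and says of the pregnancy outcome: "This will directly indicate the effectiveness of the intervention in improving fertility".

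Section 2.2.1 opens with "Participants who meet the following inclusion criteria will be included: (1) female of reproductive age 20–42 years" and goes on to BMI, regular menstruation, AMH, three further laboratory limits, consent and ability to comply. Section 2.2.2 removes some causes of failure to conceive: a low antral follicle count, repeated ovarian surgery and, at the end of the list, "6) secondary amenorrhea; (7) uterine developmental abnormalities; and (8) inability to engage in physical activity". Neither list mentions tubal patency or a partner factor.

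On who will be enrolled, section 2.6 says: "Patients meeting the eligibility criteria will be recruited from the Assisted Reproduction Center of Semmelweis University, Hungary". It tells participants that "in this clinical trial we intend to compare three groups of infertile women". The Introduction states the aim as assessing the "ovarian rejuvenating effect of this specific exercise program before IVF/ICSI cycles or spontaneous pregnancy". Section 2.5 presents pregnancy as a percentage and compares percentages by chi-square or Fisher's exact tests.

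**The concern.** A woman with bilateral tubal occlusion, or whose partner has azoospermia, meets every criterion as written. These are ordinary reasons for attending an assisted reproduction centre, and enrolment ahead of IVF/ICSI is intended. Whatever the exercise does for her ovaries, she cannot have a spontaneous pregnancy, so she adds to the denominator and never to the numerator.

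What is at stake is the reading of section 4.7. If an unknown part of each arm cannot have the event, the observed percentage mixes the effect of treatment with the make-up of the sample. A finding of no difference could then reflect who was enrolled and not the exercise programme.

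**Working it through.** **The plan's own figure.** Section 2.4 uses one-way ANOVA with three groups, f = 0.4, alpha 0.05 and power 0.95. With noncentrality λ = f²N = 0.16 × 102 = 16.32, power at N = 102 is 0.955, and the next smaller balanced total (99) gives 0.949. So 102, or 34 per group, reproduces, and 34 / (1 − 0.15) = 40 per group. This sizing is for a continuous outcome and does not cover pregnancy.

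**Inputs for pregnancy.** From the documents: 40 per arm (2.4) and Fisher's exact test (2.5). Assumed, because the documents give neither: the pregnancy rates among women able to conceive, and the share q not at risk.

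**Formula.** If a share q of each arm cannot have the event, a true rate p is observed as p(1 − q), and the difference between arms becomes (p₁ − p₂)(1 − q). At 30% versus 5% and q = 0.4 the observed rates are 0.30 × 0.6 = 18% and 0.05 × 0.6 = 3%, so a difference of 25 points becomes 15.

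**Exact power**, two-sided Fisher test at 0.05, one pair of arms, 40 per arm, no multiplicity adjustment:

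| Assumed rates | q = 0 | q = 0.2 | q = 0.4 | q = 0.6 |
|---|---|---|---|---|
| 30% vs 5% | 0.82 | 0.67 | 0.45 | 0.20 |
| 30% vs 10% | 0.53 | 0.41 | 0.26 | 0.11 |
| 20% vs 5% | 0.41 | 0.28 | 0.15 | 0.05 |
| 15% vs 5% | 0.18 | 0.11 | 0.05 | 0.02 |

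The first row is the generous one. With 34 per arm, after the plan's own dropout allowance, its 0.82 becomes 0.72.

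**False positives.** With an assumed 10% rate in both arms, the exact type I error of the same test is 0.017 at q = 0, 0.012 at q = 0.2 and 0.006 at q = 0.4. It falls as the share not at risk grows.

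**What restriction to women at risk would recover.** At 30% versus 5%:

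- q = 0.2 leaves 40 × 0.8 = 32 per arm, with power 0.68 against 0.67 diluted.
- q = 0.4 leaves 40 × 0.6 = 24 per arm, with power 0.56 against 0.45 diluted.

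The gain in power runs from almost nothing to modest. The main gain is that the percentage can be interpreted.

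**The case against.** **These women belong in the trial.** Section 2.3 sets the primary objective as ovarian function and hormone levels ahead of stimulation, and the Introduction names IVF/ICSI as one of the routes. Women with tubal or male factor are valid participants for FSH and AMH. This stands, and it argues against excluding them.

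**Randomisation deals with it.** A reader might infer that chance imbalance in the number of women not at risk could produce a false difference. The documents do not support that. Allocation is 1:1:1 at random (4.2), the test already allows for that variation, and the type I error falls. The harm is dilution, not bias.

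**Women not trying to conceive.** A reader might also infer that the trial admits women who use contraception or do not want a pregnancy. No criterion requires an attempt to conceive. But sections 2.6 and 5 describe the participants as infertile, and the Introduction defines infertility by a year of trying without contraception. That largely answers this reading. It does not answer the main one, because couples with tubal or male factor meet the same definition.

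**The article is condensed.** The full protocol or analysis plan may define the denominator for pregnancy, so its absence here is not held against the trial. The eligibility criteria, however, are given as complete numbered lists, and they set a population that does not match a stated primary outcome.

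**Pregnancy may be underpowered anyway.** At 20% versus 5%, power is 41% even if every woman can conceive. This stands, and it limits how much the eligibility gap alone can be blamed.

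**Conclusion.** The point holds in a limited form. As written, the criteria place women who cannot conceive naturally in the denominator of a primary outcome that section 4.7 treats as direct evidence of improved fertility. The rates and their difference shrink by the share of such women, and a null result for pregnancy becomes hard to interpret. No stated figure is wrong.

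The size cannot be known from the documents. At 30% versus 5% and 40 per arm, power drops by about 15 points if 20% are not at risk (82% to 67%) and by about 37 points if 40% are not (82% to 45%). Both the rates and the shares are assumptions, and smaller effects start from low power whoever is enrolled. This is a worthwhile, inexpensive improvement and ranks below an essential correction.

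**What to change.** Keep these women in the trial for FSH and AMH. Before randomisation, record for each participant whether she is able and trying to conceive naturally, using the medical history that section 2.7 already collects. State that the main analysis of spontaneous pregnancy is in the women so flagged, by randomised arm, and that the percentage among all randomised women is also reported. Qualify the sentence in section 4.7 to match.

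The flag must be fixed before allocation: the trial is open-label, and a set chosen once outcomes are known would invite selection.

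The cost is one baseline field, a short change of text and a smaller denominator for pregnancy. Little or no power is gained if few women are not at risk. Excluding these women outright would also remove the dilution, but it would narrow the population for the hormone outcomes and may slow recruitment.

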### 2.4. Sample Size

A parallel, 3-group design will be used. We determined the sample size using G*Power 3.1.9.7 software. We employed one-way analysis of variance (ANOVA) due to consideration of three different therapies. The effect size was estimated at 0.4. We set alpha to 0.05 and power to 0.95. Consequently, the software provided an estimated total sample size of 102, resulting in 34 cases per group. To account for a potential dropout rate of 15%, we increased the sample size to 40 participants per group. Therefore, the total sample size needed for the study is 120 participants [31].

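### Three unranked primary outcomes rest on one sample size calculation for a single ANOVA that names no outcome; the 0.95 power does not extend to spontaneous pregnancy

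*Protocol article*

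**What the plan says.** Section 2.3.1 of the protocol article opens with the two hormones: "The primary outcome is the change in FSH and AMH levels compared with the levels before". It then adds the binary outcome: "Spontaneous pregnancy during the study period will be recorded as a primary outcome measure". Section 4.7 repeats both designations and says of pregnancy: "This will directly indicate the effectiveness of the intervention in improving fertility". Neither section ranks the three outcomes or requires all of them to succeed.

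Section 2.4 contains one calculation. Its test is a one-way ANOVA across three therapies, and its inputs are "The effect size was estimated at 0.4" and "We set alpha to 0.05 and power to 0.95". The result is that "the software provided an estimated total sample size of 102, resulting in 34 cases per group", raised to 40 per group for 15% dropout. The effect size is not tied to FSH, AMH or pregnancy, and no pregnancy rate is given.

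Section 2.5 plans ANOVA or Kruskal–Wallis with Tukey's test for comparisons among the three groups, and chi-square or Fisher's exact tests for numbers and percentages. Tukey's test covers pairs of groups within one outcome. Nothing in the article divides alpha among the outcomes.

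**The concern.** With three primary outcomes and no order among them, a favourable result on any one can be presented as success on a primary outcome. In that case 5% is not the trial's chance of a false claim.

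The sample size serves one continuous outcome compared by ANOVA. Pregnancy is a yes/no outcome observed over about 12 weeks and falls under a different family of tests. If it stays primary, a null result will be read as failure on a primary outcome in a trial planned at 95% power, when the trial had little chance of detecting a moderate gain. The sentence in 4.7 invites that reading.

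**Working it through.** **Inputs from the article.** Three groups, effect size 0.4 (read as Cohen's f), alpha 0.05, power 0.95, N = 102, dropout 15% (section 2.4); three primary outcomes (2.3.1 and 4.7); chi-square or Fisher for percentages (2.5). **Assumed here:** all pregnancy rates, because the article gives none.

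**1. The stated sample size.** Power = P[F′(2, N − 3; λ) > F(1 − α; 2, N − 3)], with λ = N·f².
- N = 102: λ = 102 × 0.16 = 16.32, power 0.955.
- N = 99: λ = 15.84, power 0.949, so 102 is the smallest balanced size that reaches 0.95.
- Dropout: 34 / 0.85 = 40 per group, 120 in total.

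The arithmetic in 2.4 is correct.

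**2. Family-wise error if any one success counts and each outcome is tested at 0.05.**
- Three independent tests, each at exactly 0.05: 1 − 0.95³ = 0.143.
- FSH and AMH alone: 1 − 0.95² = 0.0975.
- Pregnancy tested across three groups of 34 at a 5% rate: the true size is 0.0366 (chi-square) or 0.0222 (Fisher). Then 1 − 0.95² × (1 − 0.0366) = 0.131 and 1 − 0.95² × (1 − 0.0222) = 0.118.
- Pregnancy tested by Fisher between two arms of 40 at a 5% rate: the true size is 0.004. Then 1 − 0.95² × 0.996 = 0.101.
- Simulation with all three outcomes as continuous variables correlated at 0.5 to 0.7: about 0.12 to 0.11.

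The range is roughly 10% to 14%. The top is the independence figure. Correlation between outcomes and a conservative test for a rare event both pull it down.

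**3. ANOVA power at N = 102 and f = 0.4 if alpha is divided.**

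| Alpha | Power |
|---|---|
| 0.05 | 0.955 |
| 0.025 (two outcomes) | 0.920 |
| 0.0167 (three outcomes) | 0.893 |

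**4. Power for pregnancy between two arms (two-sided Fisher's exact test at 0.05, full enumeration).**

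| Assumed rates | 34 per arm | 40 per arm |
|---|---|---|
| 5% vs 15% | 0.13 | 0.18 |
| 10% vs 20% | 0.12 | 0.16 |
| 5% vs 25% | 0.53 | 0.65 |
| 10% vs 30% | 0.44 | 0.53 |

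With 40 per arm, power of about 0.95 needs a rate near 38% against 5% (power 0.958), or 47% against 10% (0.955).

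The three-group chi-square test is less conservative but leads to the same conclusion. At 34 per group its simulated power is 0.28 for rates of 5/5/15%, 0.22 for 10/10/20% and 0.62 for 10/10/30%.

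**The case against.** The article never says that each outcome will be tested at 0.05. Alpha appears once, as an input to the sample size, and a rule for several outcomes is often left to the statistical analysis plan, which is not shown. This stands as far as it goes: the error rates above are conditional. It does not remove the point, because the choice of primary outcomes and the sample size behind them are protocol content and are stated here. A later analysis plan could divide alpha, but then the power at N = 102 would no longer be 0.95. Nor could it give pregnancy the power it lacks.

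A reader might infer that the error rate is nearly tripled. The documents do not support that as the result. The 14.3% behind it needs three independent tests, each at exactly 5%. Section 1 treats AMH and FSH as measures of the same ovarian reserve, so independence is not a natural default, and Fisher's test for a rare event runs well below 5%.

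A reader might also infer that the protocol claims 95% power for pregnancy. It does not. Section 2.4 ties the figure to an ANOVA and does not mention pregnancy. Section 2.5 says that pregnancy will be given as a percentage, and its sentence on chi-square and Fisher tests does not name it. Formal testing of pregnancy is a reasonable inference from its primary status, not stated text.

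Finally, nothing in the article links the effect size of 0.4 to AMH, so the calculation cannot be assigned to AMH on the sponsor's behalf.

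**Conclusion.** The point holds in this form: three outcomes are primary and unranked, one ANOVA was sized without naming the outcome it serves, and the only multiplicity step works among groups.

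- **Error rate.** Roughly 10% to at most about 14%, provided that any one success counts and each outcome is tested at 0.05. If all three had to succeed there would be no inflation, but no such rule is stated.
- **Pregnancy.** For a 10-point gain from a 5% rate, the power is about 0.13 to 0.18, so such a gain would be missed more than four times in five. The rates are assumptions, but power stays well short of 0.95 for every pair in the table and gets there only for very large differences. A null pregnancy result would be uninformative, contrary to the sentence in 4.7.
- **Hormones.** The design is not compromised. The sample size reproduces, and with two hormonal primaries at 0.025 the power is still 0.92 if the effect size is 0.4.

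**What to change.** - **2.3.1:** name one hormonal primary outcome, AMH or FSH at the sponsor's choice, and test the other only if the first is significant. Alternatively keep both as primary with Holm's procedure, and restate the worst-case power at alpha 0.025 as 0.92 for N = 102.
- **2.3.1 and 2.3.2:** move spontaneous pregnancy to the secondary outcomes, reported as a risk difference between arms with a confidence interval.
- **2.4:** state which outcome the effect size of 0.4 and the power of 0.95 refer to.
- **2.5:** state the chosen order or the Holm rule.
- **4.7:** remove the primary label from pregnancy and replace the sentence on direct effectiveness with one that says the comparison is not powered.

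The cost is wording. Pregnancy loses its primary status and, under Holm, the stated power is slightly lower. No extra patients are needed. The change should be made before outcome data are seen, the more so because the trial is open-label.
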